The sample size for this study was determined using the GRANMO program with the model of observed proportions with respect to a reference. For the calculation, it has been taken into account that the insulin resistance is the key to calculating the effects of aerobic and resistance training on clinical parameters in patients with T2D. The calculation has been made accepting an 𝜶 risk of 0.05 and a beta risk of less than 0.2 in a two-sided contrast. Based on preliminary data, there is a difference of HOMA-IR of -0.14% after 12 weeks of intervention (21). Although modest, this effect size has been reported as clinically relevant in previous clinical trials (22–24). It is assumed that the proportion in the reference group is 0.0139 (5.3 million people in Spain) (25). The percentage of necessary replacements has been predicted to be 20%. The present study is designed as an exploratory factorial randomized clinical trial; while not powered for a definitive test of interaction effects, the chosen sample size allows us to detect main effects with adequate power while providing preliminary evidence of potential interactions.

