### Statistical analysis

2.11

All data will be reported as mean and standard deviation. Data normality and homogeneity of variance will be tested using Shapiro–Wilk and Levens tests, respectively. The primary endpoint (change in HOMA-IR) from baseline to 16 weeks, will be analyzed using ANCOVA with group as the fixed factor, baseline HOMA-IR as covariate, and VitD treatment status included as a stratification variable. Secondary continuous outcomes (glycemic, lipid, inflammatory, anthropometric, dietary, and psychological well-being measures) will also be analyzed with ANCOVA, adjusting for baseline values. Categorical outcomes (e.g., adverse events) will be compared using χ^2^ or Fisher’s exact test. Bonferroni *post hoc* test will be used if there is a significant difference between the groups. Exploratory analyses will test for interaction effects between exercise and VitD status using factorial ANOVA models; these analyses are considered hypothesis-generating due to sample size limitations. In addition, exploratory analyses will be performed to examine potential sex-related differences in primary and secondary outcomes. Sex will also be included as a covariate in the statistical models when appropriate. Statistical power will be calculated by *post hoc* power analysis method by using G Power software.

The results will be analyzed using SPSS (version 22) for Windows. The significant level (*α*) of all statistical analyses will be 0.05.

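### Section 2.11 plans a post hoc power calculation with no effect size named; on its natural reading it only re-expresses the p-value

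*Protocol article*

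**What the plan says.** Section 2.11 (Statistical analysis) lists ANCOVA for the primary and secondary continuous outcomes, chi-square or Fisher tests for categorical outcomes, Bonferroni comparisons, and exploratory interaction and sex analyses. It then says that power will be calculated by a post hoc "power analysis method by using G Power software". It does not say which effect size will be entered, for which test, or how the result will be used.

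The same section gives the reporting rule "All data will be reported as mean and standard deviation" and sets the significance level "of all statistical analyses will be 0.05".

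The planning inputs are in section 2.2 (Participants):
- The error rates are an alpha "risk of 0.05 and a beta risk of less than 0.2 in a two-sided contrast".
- The model is that of "model of observed proportions with respect to a reference".
- The effect is that "there is a difference of HOMA-IR of -0.14% after 12 weeks of intervention".

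No SD of HOMA-IR or of its change is given. The section also says that main effects can be detected with adequate power and that the trial is not powered for a definitive interaction test.

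**The concern.** A power calculation informs when the effect entered is chosen without looking at the result. If the effect entered is the one just estimated, the calculation takes the test statistic as its input and returns the p-value on another scale. A non-significant result then always shows low power and a clearly significant one higher power, whatever the true effect and however large the trial.

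This trial has 80 participants, calls itself exploratory, and says that its findings could inform guidelines. If the primary HOMA-IR comparison is not significant, readers will want to know whether the trial was too imprecise to tell or whether it excludes an effect worth having. A post hoc power figure looks like an answer to that question. Computed from the observed effect, it is not one.

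**Working it through.** The article states no post hoc power figure, so there is none to reproduce. The check asks what the planned calculation would return.

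**Inputs**
- Two-sided alpha 0.05 (sections 2.2 and 2.11).
- N = 80 in four groups of 20, so 40 exercise and 40 no exercise (section 2.2, Table 1). Full retention is assumed.
- Primary model: ANCOVA with four-level group and baseline HOMA-IR (section 2.11). VitD status is fixed by group and takes no further degree of freedom. Residual df = 80 − 4 − 1 = 75.
- Effect size: none named in section 2.11. Section 2.2 gives −0.14% with no SD under a proportion model, so it yields no standardized effect for the ANCOVA. The only effect then available is the observed one.

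**Two-group contrast, 75 df**

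Observed power = P(|T′| > 1.992), where T′ is noncentral t with 75 df and noncentrality equal to the observed |t|. Since |t| is fixed by p, so is the power.

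| p | observed \|t\| | observed power |
|---|---|---|
| 0.01 | 2.643 | 74% |
| 0.05 | 1.992 | 50% |
| 0.10 | 1.665 | 38% |
| 0.20 | 1.293 | 25% |
| 0.50 | 0.678 | 10% |

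**Four-group F test, 3 and 75 df**

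Observed power = P(F′ > 2.727), where F′ is noncentral F. Two conventions for the noncentrality are in use: λ = 3F, or λ = f² × 80 with f² = 3F/75.

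| p | observed F | λ = 3F | power | λ = f² × 80 | power |
|---|---|---|---|---|---|
| 0.05 | 2.727 | 8.18 | 64% | 8.73 | 67% |
| 0.20 | 1.585 | 4.76 | 40% | 5.07 | 43% |
| 0.50 | 0.796 | 2.39 | 21% | 2.55 | 23% |

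The convention moves the figure by 1 to 3 points. Either way, any p above 0.05 gives a value below the 80% implied by the planning beta.

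**Does the figure respond to precision?**

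Hold p = 0.30 and vary the number per group in a simple two-group comparison. With SE = √(2/n) in SD units, the estimate is t × SE and the 95% CI is (t ± t₀.₉₇₅) × SE.

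| n per group | observed power | estimate (SD) | 95% CI (SD) |
|---|---|---|---|
| 10 | 17% | 0.48 | −0.46 to 1.42 |
| 40 | 18% | 0.23 | −0.21 to 0.68 |
| 4000 | 18% | 0.02 | −0.02 to 0.07 |

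Observed power hardly moves. The interval goes from one that excludes almost nothing to one that excludes any effect above 0.07 SD.

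**The alternative reading**

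If an effect fixed in advance is entered, the link to p is broken. At 40 versus 40, a standardized difference of 0.5 gives 60% power and 0.8 gives 94%, whatever p turns out to be. The article names no such effect.

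**The case against.** The strongest reply is that the article never says the observed effect will be used. G*Power's post hoc mode also accepts an effect chosen in advance, and the last step above shows that the criticism would then fail. This stands as a limit: observed power is an inference from the missing effect size and SD and from the sentence's place among the analyses of results. It does not rescue the sentence, which on the other reading still leaves out the one input that would make it meaningful.

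Three stronger readings are tempting and are not supported:
- A reader might infer that the plan will label null results underpowered or use the figure to excuse them. Neither section 2.11 nor the discussion or limitations says so. The risk lies in how the number may be read.
- A reader might take the absence of confidence intervals as a defect in itself. The rule "All data will be reported as mean and standard deviation" is a descriptive-summary rule and does not exclude intervals from the ANCOVA. A condensed article may leave that presentation to an analysis plan that is not shown. Intervals enter here only as the remedy.
- A reader might take exercise versus no exercise as the main comparison. The introduction and section 2.1 state the superiority hypothesis for the combination against exercise alone, VitD alone and control, so a change to the power sentence should not settle that question. The two-group figures above hold for any single contrast on 75 df and imply no choice among them.

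It is also fair to say that the sentence alters no test, estimate, alpha level or sample size. That limits the weight of the point.

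**Conclusion.** The point holds in a limited form. Section 2.11 commits to a post hoc power calculation without naming its effect size, and section 2.2 supplies no SD or standardized effect to fill the gap. On the natural reading the result restates the p-value: about 50% at p = 0.05 and 25% at p = 0.20 for a single contrast, and about 64–67% and 40–43% for the four-group F test. It cannot separate an uninformative null from one that rules out a relevant HOMA-IR effect.

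This rests on three assumptions: the observed effect is entered, all 80 participants are analysed (75 residual df), and alpha is 0.05 two-sided. Dropout would change the df, but power would still be fixed by p. The effect is on interpretation only; the validity of the primary test is untouched. The sentence is worth correcting because a better quantity is available at almost no cost.

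**What to change.** Delete the post hoc power sentence from section 2.11. In its place, state that the baseline-adjusted between-group differences from the planned ANCOVA will be reported with 95% confidence intervals, for the contrasts the protocol already specifies. The wording should leave the primary contrast as it stands.

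If a power statement is kept, it should name a HOMA-IR difference and an SD fixed before data are seen, and the test to which it applies.

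The cost is one sentence replaced. The intervals come from the same ANCOVA fit. Design, data collection and conduct do not change.

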## Discussion

3

The DIAVITEX study addresses a relevant clinical question of two widely recommended interventions for T2D: physical exercise and VitD supplementation. While both have shown independent benefits on insulin resistance, glycemic control, and cardiovascular health, few studies have evaluated their combined effects in a rigorously controlled, randomized clinical trial. This study is among the first to investigate their potential synergistic impact in a well-characterized cohort of T2D patients under real-world treatment regimens.

Previous literature has demonstrated that structured aerobic and resistance training significantly improve cardiorespiratory fitness and reduce HbA1c levels in patients with T2D (6). Similarly, low serum VitD levels are associated with impaired glucose metabolism and increased T2D risk (16). However, evidence regarding the effects of VitD supplementation alone has been inconsistent, particularly in individuals with normal baseline VitD status. Notably, few clinical trials have jointly evaluated these two strategies, and those that have done so often suffer from small sample sizes, limited outcome measures, and short intervention durations (20, 21).

DIAVITEX contributes to this knowledge gap by employing a factorial design that enables the comparison of exercise-only, VitD-only, combined, and control groups. By incorporating a broad range of clinical endpoints (including metabolic markers, inflammatory biomarkers, body composition, psychological well-being, and dietary adherence) the study offers a holistic perspective on the intervention effects. Additionally, the integration of pharmacists and primary care professionals reflects a translational approach that could facilitate future implementation in community settings.

An innovative aspect of this study is the delivery of the exercise program in a home-based, online format, which enhances accessibility and scalability. While this design reduces logistical barriers, it also introduces variability in adherence and exercise quality, which will be monitored, as discussed in the limitations. Importantly, all participants will receive standardized dietary advice to reduce confounding effects from uncontrolled nutritional factors.

The findings of this study have the potential to inform evidence-based clinical guidelines and public health policies by identifying whether combining exercise with VitD supplementation provides additive or synergistic benefits beyond either intervention alone. If successful, DIAVITEX could help justify broader recommendations for personalized, integrative care models in T2D management.

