Few studies evaluated the effects of VitD and PA in patients with T2D. Kim et al. showed that the combination had positive effects on abdominal fat and blood lipid profiles, but the metabolic characterization of these patients was limited, and results were inconclusive (19). Dadrass et al. showed that VitD supplementation, in addition to resistance training, had positive effects on some inflammatory markers (interleukin 6, tumor necrosis factor *α* and C-reactive protein) in men with T2D and VitD insufficiency but they did not analyze any non-inflammatory metabolic parameters (20). In conclusion, although some studies link VitD and aerobic or endurance exercise to improved T2D outcomes, the analyses are scattered and inconsistent, with incomplete metabolic characterization, low numbers of patients, and generally unreliable conclusions.

To overcome these limitations, the DIAVITEX study employs a randomized factorial design with a larger sample size and stratification by VitD treatment status, allowing the independent and combined effects of exercise and VitD to be assessed. It also incorporates a comprehensive metabolic characterization (including insulin resistance, glycemic, lipid, and inflammatory biomarkers) and a 16-week structured, supervised exercise program to ensure adherence and reproducibility. Involving pharmacists and primary care professionals further enhances safety and translational applicability in real-world clinical settings.

The DIAVITEX study aims to identify the effect of aerobic and resistance training in T2D patients on a VitD regime and to compare them with patients not exercising or not on VitD therapy, in order to provide evidence for optimizing disease management. The specific objectives are to evaluate the effect of aerobic and resistance training, with or without VitD treatment, on:

Insulin resistance (primary endpoint: HOMA-IR).Glycemic, lipid, inflammatory and renal biomarkers.Anthropometric measures.Adherence to the Mediterranean diet.Psychological well-being among patients with T2D before and after the intervention.The role of the pharmacist in patient follow-up including medication monitoring, intervention support, and safety oversight during the trial (exploratory process outcome).

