### Participants

2.2

The study will include a total of 80 individuals of both sexes (female, male) with a diagnosis of T2D. Among them, 40 individuals will be required to be on a VitD treatment for at least, 6 months, for reasons recommended by the ECAP working group (including osteoporosis, osteopenia, and VitD deficiency), and the other 40 will not be receiving VitD supplementation.

Subjects will be recruited during usual medical care in a convenience-based by the collaborating physician from the Primary Care Center (CAP) Sant Rafael in Barcelona, Spain.

During the initial visit with the physician at CAP Sant Rafael, participants will be provided with the Patient Information Sheet and the Informed Consent and subsequently will be asked to provide their preferred contact information (phone number or email). This information will be used by the principal investigators from Blanquerna to reach out explaining the study with detailed instructions (explaining the patient information sheet and address any questions they may have). After receiving the information and clarifying any potential concerns, participants will be asked to sign the informed consent.

After enrollment and stratification by VitD treatment status, participants will be randomized within each stratum to exercise intervention or to no exercise. An independent investigator, not involved in recruitment or outcome assessment, will generate the randomization sequence using a computer-based block randomization method within VitD strata. Allocation will be implemented via a secure, web-based central randomization system accessible only after completion of baseline assessments and confirmation of eligibility. This ensures that the four groups (see Table 1) are balanced and clearly defined as: Group 1, Exercise + VitD users; Group 2, Exercise + VitD non-users; Group 3, VitD only (no exercise); and Group 4, Control (no VitD & no exercise).

**Table 1 tab1:** Group allocation of participants with T2D.

Group	VitD treatment status	Exercise intervention	*n*
1	On VitD ≥ 6 months	Exercise program	20
2	No Vit D treatment	Exercise program	20
3	On VitD ≥ 6 months	No exercise	20
4 (Con)	No Vit D treatment	No exercise	20

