#### Primary endpoint

2.4.1

The primary endpoint of the DIAVITEX trial is the change in insulin resistance, measured by the HOMA-IR index, from baseline to week 16.

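### VitD use predates baseline by at least 6 months and is not randomized, so the baseline-adjusted HOMA-IR contrasts between VitD users and non-users do not test VitD benefit or additivity

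*Protocol article*

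**What the plan says.** **Exposure and randomization.** Section 2.2 (Participants) states that "40 individuals will be required to be on a VitD treatment for at least, 6 months"; the other 40 take none. After stratification by VitD status, "participants will be randomized within each stratum to exercise intervention or to no exercise". VitD is ongoing treatment, and the article describes no planned start or change of it during the 16 weeks.

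**Endpoint and model.** The primary endpoint (2.4.1) is "the change in insulin resistance, measured by the HOMA-IR index, from baseline to week 16". Under 2.11 it "will be analyzed using ANCOVA with group as the fixed factor, baseline HOMA-IR as covariate, and VitD treatment status included as a stratification variable".

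**What is claimed for VitD.**
- Section 1 (Introduction) presents the design as "allowing the independent and combined effects of exercise and VitD to be assessed".
- The hypothesis that closes section 1, and the superiority statement in 2.1, put the combination ahead of exercise alone, VitD alone and control.
- Section 3 (Discussion) cites the design as "employing a factorial design that enables the comparison of exercise-only, VitD-only, combined, and control groups" and expects to learn whether "combining exercise with VitD supplementation provides additive or synergistic benefits beyond either intervention alone".

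**What is disclosed.** Section 3.1 (Limitations) treats patients already on VitD as a recruitment matter and discusses seasonal VitD levels. It does not say that a VitD effect may already be contained in the baseline value. Sections 2.2 and 2.11 describe the factorial trial as exploratory and its interaction analyses as hypothesis-generating.

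**The concern.** Between baseline and week 16, Group 3 (VitD, no exercise) is assigned nothing that Group 4 (neither) is not. If VitD and exercise act additively and the VitD effect is already established, Group 1 (both) and Group 2 (exercise only) have the same expected change. The endpoint measures what happens after baseline, whereas the claims concern a treatment begun at least 6 months before it.

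Two misreadings follow. A null result for Group 3 vs 4 or Group 1 vs 2 could be reported as VitD adding nothing, although the analysis registers only part of an established effect. A non-null result could be reported as VitD benefit, although an ordinary baseline difference between users and non-users gives the same figure. The Discussion offers these conclusions for guidelines and public health policy.

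The attenuation is separate from confounding: it would remain if users and non-users were perfectly comparable.

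**Working it through.** **Inputs from the article:** 20 per group; VitD for at least 6 months before baseline in Groups 1 and 3; change in HOMA-IR at week 16; ANCOVA on group and baseline; two-sided 0.05. The article gives no SD, no baseline to week-16 correlation and no expected VitD effect, so it has no figure of its own to reproduce on this point.

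**Assumptions:** SD 1 at both times; correlation r from 0.5 to 0.8; VitD effect τ = −0.5 SD, fully present at baseline and persisting; no interaction with exercise. V = 1 for VitD users, E = 1 for exercise, and δ is the exercise effect.

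**1. Model.** Y0 = τV + e0 and Y16 = τV + δE + e1, with corr(e0, e1) = r.

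**2. Change score.** E[Y16 − Y0] = δE. The VitD term drops out, so Group 3 − Group 4 and Group 1 − Group 2 both have expectation 0.

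**3. Planned ANCOVA.** E[Y16 | Y0, V, E] = τV + δE + r(Y0 − τV) = (1 − r)τV + δE + rY0. The VitD coefficient is (1 − r)τ. It is the same whether the outcome is change or the week-16 value, because baseline is a covariate. Adding VitD status as a further term does not alter this, since group already determines VitD status.

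**4. Power.** SE = sqrt(2(1 − r²)/n) with n per side. For r = 0.5 and n = 20, SE = sqrt(2 × 0.75/20) = 0.274 and 0.25/0.274 = 0.91, giving 15%. The last two columns show, for scale, the same −0.5 SD arising wholly after baseline.

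| r | Expected contrast (SD) | Share of τ | Power, 20 vs 20 | Power, pooled 40 vs 40 | After baseline, 20 vs 20 | After baseline, 40 vs 40 |
|---|---|---|---|---|---|---|
| 0.5 | −0.25 | 50% | 15% | 25% | 45% | 73% |
| 0.7 | −0.15 | 30% | 10% | 16% | 60% | 88% |
| 0.8 | −0.10 | 20% | 8% | 12% | 75% | 96% |

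A simulation of the planned ANCOVA with 20 per group (3,000 runs per scenario) agreed. Group 1 − Group 2 averaged −0.253, −0.145 and −0.100 for the three values of r, with rejection rates of 14.2%, 9.8% and 7.5%. The mean Group 3 − Group 4 change difference lay within 0.01 of zero.

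**5. Does the residual identify VitD?** If users also differ from non-users by c at baseline for other reasons, the coefficient becomes (1 − r)(τ + c). At r = 0.7:
- τ = −0.5, c = 0 gives −0.15.
- τ = 0, c = −0.5 also gives −0.15.
- τ = −0.5, c = +0.5 gives 0.

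The first two cases cannot be separated, and the third hides a real effect.

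**6. If the effect is still accruing.** With a fraction f in place at baseline, the change contrast is (1 − f)τ and the ANCOVA contrast is τ(1 − rf). For f = 0.5 the change contrast is −0.25. The ANCOVA contrast is −0.5 × 0.75 = −0.375 at r = 0.5 and −0.5 × 0.60 = −0.30 at r = 0.8. Part of the effect then shows.

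**7. What survives.** Group 1 vs 3 and Group 2 vs 4 are randomized within VitD strata and estimate δ. Their difference estimates how the exercise effect varies with VitD use; in the simulation it averaged within about 0.02 of zero where no interaction had been built in.

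**The case against.** **The aim is narrower than the claims.** The abstract asks about exercise in patients already taking VitD, and randomization within strata answers that. Gain over VitD alone (Group 1 vs 3) is a clean randomized contrast, and synergy survives as effect modification, already labelled exploratory. All of this stands. It confines the problem to the independent and additive VitD claims and to superiority over exercise alone.

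**The analysis is not blind to VitD.** A reader might infer that no VitD effect can appear, or that the contrasts must be near zero even if VitD works. The documents do not support that: zero applies to unadjusted change, while the planned model is ANCOVA, which keeps 20% to 50% on the assumed r.

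**Steady state is assumed.** The documents give no time course, and an effect still building after 6 months would show in part. Section 3.1 also says that VitD levels vary with sun exposure, especially without supplementation, so users and non-users may diverge during follow-up. It would therefore go too far to say that nothing about VitD changes over the 16 weeks, or that any non-zero difference is only a baseline artefact. Effect modification, accrual and seasonal divergence are other possible sources. None of them turns the contrast into a test of VitD benefit.

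**The fair comparison is pooled.** Under additivity the VitD contrast can use 40 vs 40, where power is 25% to 12% instead of 15% to 8%. It is still low.

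**Conclusion.** The concern holds in limited form. The article credits the design with a property that it lacks: the ability to assess an independent or additive VitD effect through baseline-adjusted change in HOMA-IR. A VitD effect established by baseline cancels in change scores and is reduced to 1 − r of its size in the planned ANCOVA. There it is mixed with whatever else distinguishes users from non-users. On the assumed −0.5 SD and r of 0.5 to 0.8, that leaves −0.25 to −0.10 SD.

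The direction of the result rests on the article's own exposure timing, endpoint and model. Its size rests on the assumed effect, the assumed correlation and steady state by 6 months.

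Group 3 vs 4 and Group 1 vs 2 should therefore not be read, whether null or not, as tests of VitD benefit or additivity. The trial as a whole is not undermined: the randomized exercise contrasts and the exploratory question of effect modification remain valid.

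**What to change.** - **2.11:** state that the primary analysis estimates the exercise effect on HOMA-IR and, as exploratory, whether that effect differs by VitD use. State that contrasts between VitD users and non-users (Group 3 vs 4, Group 1 vs 2) are not tests of VitD benefit or additivity.
- **Section 1 (hypothesis) and 2.1 (superiority statement):** reword to match, so that superiority is claimed for exercise within VitD strata and not for the combination over exercise alone.
- **Section 1 (design paragraph) and section 3:** replace the independent, combined, additive and synergistic claims with the question of whether the exercise effect on HOMA-IR differs between VitD users and non-users.
- **3.1:** add that a VitD effect may be largely contained in baseline, and that VitD use was not randomized.

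A comparison of baseline HOMA-IR between the 40 users and 40 non-users would not rescue the VitD claim. Section 2.2 says VitD is given for osteoporosis, osteopenia and deficiency, so users differ by indication, and adjusting for age, sex and BMI would not isolate a VitD effect.

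The cost is wording only: no change to randomization, visits, measurements or sample size. What is given up is the VitD-only and additivity conclusions.
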